### Primary outcome

The primary outcome is 24 week continuous abstinence (Russell Standard) defined as self-report of smoking not more than five cigarettes from the randomisation date, supported by biochemical validation (eCO reading using a Bedfont Smokerlyser CO Monitor, with a reading of ≤10 ppm signifying abstinence). Sensitivity analysis will be undertaken looking at different cut-offs for the CO measurement, given a lack of consensus about the best cut-off to use [48, 49].

### Secondary outcome measures

The following secondary outcome measures will be assessed at randomisation, then at six, 12 and 24 weeks post-randomisation (Table 1):*Continuous abstinence (6 and 12 weeks)*: The proportion of participants that have stopped smoking defined as smoking not more than five cigarettes in total from randomisation (self-reported) (biochemically validated using a CO reading of ≤10 ppm at 24 weeks);*Seven-day point prevalence abstinence*: The proportion of participants that have stopped smoking, defined as self-report of smoking no cigarettes at all, not even a single puff in the last seven days;*Time to first lapse*: Defined as time to first cigarette smoked, even a single puff;*Time to first relapse*: Defined as time to smoking more than five cigarettes a day for three or more days in a row;*Change from randomisation in cigarettes smoked per day*: If the participant is still smoking;*Smoking reduction*: Defined as reducing consumption by ≥50% (in terms of numbers of cigarettes per day, weight of loose tobacco per day, or when smoking for non-daily smokers);*Change from randomisation in the physical signs and symptoms associated with withdrawal (randomisation and 6 weeks)***:** Measured using the Mood and Physical Symptoms Scale (MPSS) [47], including urge to smoke;*Concomitant medication*;*Use of any other smoking cessation methods*: NRT, non-NRT methods of cessation such clonidine, nortriptyline, acupuncture, Quitline, etc.;*Alcohol and drug use/severity of AOD problems (12 and 24 weeks only)*: Measured using the ASSIST-FC [45];*Mental health symptoms*: Measured using the K6 [46];*Health-related quality of life (randomisation and 24 weeks only):* Measured using the NZ EQ-5D Tariff 2 (telephone script) [50];*Confidence in ability to quit (randomisation only):* Measured on a Likert scale of 1 to 5, where 1 = ‘not very’ and 5 = ‘very’;*Adverse events*: Information regarding adverse events and whether they are related to treatment;*Medication compliance (randomisation, 6 and 12 weeks):* Self-reported frequency of using allocated product;*Crossover*: Participants in the varenicline only or varenicline + bupropion groups will be asked whether they accessed and used an EC (with or without nicotine) in the follow-up period;*Additional EC support (6 and 12 weeks):* Participants allocated to the varenicline + EC group will be asked whether they accessed any (on-line) EC support networks or bought different e-juice or EC during the trial;*Dual use (6 and 12 weeks):* Defined as use of both their allocated treatment and continued smoking of cigarettes;*Continuation of use (24 weeks):* Defined as continued use of their allocated treatment after the end of the designed 12 week treatment period;*Perception of the product (24 weeks only):* Participants will be asked for their views on use of their allocated treatment as a smoking cessation aid;*Acceptability/Recommendations* (*24 weeks only):* Participants will be asked whether they would recommend their allocated treatment to another smoker who wanted to quit.

### Sample size

A sample size of 338 (169 in each arm) anticipates a 30% loss-to-follow-up and will confer 80% power, 2-sided *p* = 0.05 to detect an absolute difference of 15% between the varenicline plus EC group and varenicline alone group in 24 week carbon monoxide (≤10 ppm) verified abstinence rates, with a predicted abstinence rate in the varenicline plus EC group of 30%. The anticipated 30% loss-to-follow-up is more than the 22% noted in the psychiatric cohort in the EAGLES trial [14] but lower than the 39% found in the Ebbert et al. trial [38]. We estimate 30% of participants will collect and use the prescribed varenicline for the first 2 weeks of the study [51], and that most (around 80%) of this group will be varenicline non-responders after 2 weeks of medication use [23]. Thus, 507 people will need to be recruited into the ‘initial treatment phase’ in order to obtain 338 people to be randomised. We anticipate it will take 16 months to recruit 338 participants.

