**Methods:**

This is a pragmatic two-arm, open-label, randomised trial. Participants will be daily smokers using mental health and/or addiction services in Auckland, aged ≥18 years, motivated to quit smoking, and eligible to access varenicline through the NZ special authority process. After 2 weeks of using varenicline plus behavioural support, participants who have not reduced their daily smoking by ≥50% will be randomised (1:1) to either 10 weeks of continued varenicline use or 10 weeks of varenicline plus an 18 mg/mL nicotine e-cigarette. All participants will receive weekly withdrawal-orientated behavioural support calls for 6 weeks post-randomisation. The primary outcome is self-reported biochemically-verified (exhaled carbon monoxide) continuous abstinence at 24 weeks post-randomisation. Secondary outcomes, measured at six, 12 and 24 weeks post-randomisation include: self-reported continuous abstinence, 7-day point prevalence abstinence, smoking reduction, time to relapse, cross-over, use of other smoking cessation support, serious adverse events, treatment adherence, compliance, acceptability, dual use, continuation of treatment use, mental illness symptoms and AOD use, health-related quality of life, and cost-analysis. A sample size of 338 will confer 80% power (*p* = 0.05) to detect a 15% absolute difference between the varenicline alone and varenicline plus e-cigarette groups.

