### Statistical analysis

All statistical analyses will be performed using SAS version 9.4 (SAS Institute Inc. Cary NC), and R [53]. Analyses will be undertaken on an intention-to-treat basis. For the main analyses, all participants lost to follow-up will be presumed to be smoking. Per-protocol analysis will be undertaken for the primary outcome where participants with major protocol violations (e.g. cross-overs treatments, withdrawals, and loss to follow-up) will be excluded. Sensitivity analyses will be carried out to determine the effect of missing data and if the level of missing data is deemed high (i.e. > 20%) use of multiple imputation will be employed. Participant flow through the trial will be described in a Consolidated Standards of Reporting Trials (CONSORT) diagram. The number of withdrawals will be summarised by type, treatment group and time, with reasons where provided. Incidence rates, risk difference, RR and 95% CI will be calculated for all binary outcomes, and groups will be compared using chi-squared tests and multiple logistic regression analysis where appropriate. Continuous outcomes will be analysed using multiple linear regression modelling or non-parametric analysis. K6 and change in cigarettes smoked per day (in non-abstainers) will be analysed using repeated measures models, and will adjust for baseline value. Time to relapse will be analysed using Kaplan Meier curves, log-rank test, and Cox proportional hazards regression analysis. Secondary analyses will be conducted to determine the impact of varying cut-offs used for CO measurements, and secondary analyses performed with cessation rates corrected for discordance between reported and CO-verified cessation. The consistency of effects for pre-specified subgroups will be assessed using tests for heterogeneity. Subgroups will be based on sex, ethnicity, and type of cigarette.

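### The 80% power at 338 belongs to an analysis that drops the lost; the main analysis counts them as smokers, and there the power is about 92% or about 76%, depending on an unstated scale

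*Protocol article*

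**What the plan says.** The Sample size section of the protocol article gives the target: "A sample size of 338 (169 in each arm) anticipates a 30% loss-to-follow-up and will confer 80% power". The test is two-sided at 0.05 and the aim is "to detect an absolute difference of 15% between the varenicline plus EC group and varenicline alone group", measured as CO-verified abstinence at 24 weeks. The predicted rate with the e-cigarette is 30%, so the rate on varenicline alone is taken as 15%. The same section sets the 30% loss beside 22% and 39%, the losses it reports from two other trials. The Methods paragraph of the abstract repeats the claim without the loss allowance: "A sample size of 338 will confer 80% power".

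The Statistical analysis section makes the analyses intention to treat and adds: "For the main analyses, all participants lost to follow-up will be presumed to be smoking". Exclusion of the lost is named there only for the per-protocol analysis of the primary outcome.

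**The concern.** Dividing by one minus the loss rate compensates for people who disappear from the analysis. Under the main analysis nobody disappears. All 338 stay in the denominator, and loss acts on the abstinence rates instead, because each lost participant is counted as a failure. The sample size section and the analysis section therefore treat the same 30% in two incompatible ways.

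What is at stake is the headline power of the primary outcome and the benchmark for reading its result. A reader who is told 80% power for 15 points cannot tell whether the primary analysis has more power than that, or has less and expects a smaller difference. The article never says whether 15% and 30% are rates among everyone randomised or among those followed up.

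**Working it through.** **Inputs.** From the Sample size section: 169 per arm, 30% loss, 80% power, two-sided 0.05, a 15-point difference and 30% in the e-cigarette arm. The 15% in the other arm follows by subtraction. From the Statistical analysis section: all randomised are analysed, the lost are counted as smoking, and groups are compared by chi-squared test.

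**Step 1: reproduce the plan's figure.** Per-arm size with unpooled variance:

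n = (1.96 + 0.842)² × [0.30 × 0.70 + 0.15 × 0.85] / 0.15² = 7.849 × 0.3375 / 0.0225 = 117.7, so 118.

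Allowance for loss: 118 / 0.70 = 168.6, so 169 per arm and 338 in total. The match is exact. The pooled-variance formula gives 121 per arm and 346 in total after inflation. The 80% is thus the power of a comparison of about 118 followed-up people per arm with the lost removed.

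**Step 2: power of the main analysis if 15% and 30% already count the lost as smoking.** All 169 per arm are analysed at these rates.

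- Unpooled: SE = √(0.3375 / 169) = 0.0447; 0.15 / 0.0447 − 1.96 = 1.40; power 91.9%.
- Pooled: 91.4%. Exact enumeration of the chi-squared test: 91.8%.
- For 80% power, 118 to 121 per arm (236 to 242 in total) would be enough, with no inflation.

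**Step 3: power of the main analysis if 15% and 30% are rates among those followed up.** Assume equal 30% loss in both arms. The analysed rates become 0.70 × 15% = 10.5% and 0.70 × 30% = 21%, a 10.5-point difference.

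- Unpooled: SE = √[(0.21 × 0.79 + 0.105 × 0.895) / 169] = √(0.2599 / 169) = 0.0392; 0.105 / 0.0392 − 1.96 = 0.72; power 76.4%.
- Pooled: 75.7%. Exact: 76.5%.
- For 80% power, 186 to 188 per arm (372 to 376 in total) would be needed.

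**Step 4: sensitivity of step 3 to the loss rate**, using the two other rates in the Sample size section (pooled formula, 169 per arm, equal loss in both arms):

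| Loss | Analysed rates | Power |
|---|---|---|
| 22% | 11.7% vs 23.4% | 81% |
| 30% | 10.5% vs 21% | 76% |
| 39% | 9.15% vs 18.3% | 69% |

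At the planned 30% loss, neither reading gives 80%.

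**The case against.** The arithmetic in the Sample size section is correct in itself: 338 follows from its inputs. What is at fault is the fit between two sections, not a calculation.

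The more natural reading may also be the favourable one. The section describes abstinence rates by randomised group on the primary outcome and nowhere limits them to people followed up. Together with the lost-as-smoking rule, that suggests 15% and 30% are the rates to be analysed. Power is then about 92%, and the loss allowance is merely generous. This objection stands as far as it goes: the documents do not show an underpowered trial. It does not rescue the stated 80%, and the text does not settle the scale. The allowance itself makes sense only for an analysis that excludes the lost, which points the other way.

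The 76% is also conditional. It needs equal loss in both arms and loss at the planned 30%; at 22% loss the power would be 81%. That is a fair limit on the size of the shortfall, which is about 4 points at the planned loss.

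A reader might further see a conflict in the multiple-imputation rule: "if the level of missing data is deemed high (i.e. > 20%) use of multiple imputation will be employed", a threshold below the planned 30%. The documents do not support that. Imputation is placed among the sensitivity analyses, whose purpose is to try a different assumption about missing data. A threshold that will probably be met only means that this analysis will probably be run.

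**Conclusion.** The point holds as a mismatch between the Sample size and Statistical analysis sections. The stated 80% belongs to an analysis that removes the lost, and so does not describe the primary analysis. For the primary analysis at 169 per arm, power is about 91 to 92% if 15% and 30% are on the lost-as-smoking scale. It is about 76% for 10.5% against 21% if they are rates among those followed up. The second figure assumes 30% loss in each arm and ranges from 81% to 69% at the other two loss rates the section cites.

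A reader might infer that the main analysis cannot show a 15-point difference. The documents do not support this. On the first reading the main analysis targets exactly 15 points. On the second, 10.5 points is only the expected difference, under the stated rates and equal loss. Nor do they support the inference that more participants are required, because the scale is left open.

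**What to change.** In the Sample size section, state which scale the 15% and 30% are on, and restate the power and the detectable difference for the main analysis to match:

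- Rates among all randomised, with the lost counted as smoking: 338 gives about 92% power for a 15-point difference, and no loss inflation applies.
- Rates among those followed up: with 30% loss in each arm, 338 gives about 76% power for 10.5% against 21%, a 10.5-point difference in the main analysis.

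Correct the power statement in the abstract in the same way. The lost-as-smoking rule and the place of imputation can stay as they are. The cost is a few words and one recalculated figure in two places; the sample size need not change.

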In NZ nicotine is regulated as a medicine, except when delivered in tobacco smoke. Currently it is illegal to sell an EC that contains nicotine or to make a cessation claim about ECs, because Medsafe (the authority for licensing medicines) consider ECs as medicines when they are supplied for use as an aid to smoking cessation or when supplied with nicotine (even if they are not represented as aids to smoking cessation). Furthermore, they are not therapeutic products when they are supplied as a “gadget” which consumers may choose to use as a social prop or as an item which is to be used interchangeably with cigarettes. However, in late March 2017, the Ministry of Health announced their plans to legalise the sale and supply of EC and e-liquid to happen from the middle of 2018 [31].

The STATUS trial involves ‘boosting’ treatment in people with mental illness and/or AOD addictions if no response is seen to the initial treatment within 2 weeks. The rationale for this design is based on the finding that smokers who reduce their cigarette consumption by at least 50% during the first 2 weeks after starting on either varenicline or NRT (hereafter, ‘responders’) are 2 to 3 times more likely to quit for the long-term than smokers who do not experience this positive medication response (‘non-responders’) [23, 32–34]. This increased chance of quitting is thought to result from more the rapid de-conditioning of nicotinic-receptor-mediated dopamine reinforcement from cigarette smoke among responders; NRT is a full agonist at most nicotinic receptors and varenicline a partial agonist at the receptor thought to be most important for cigarette reinforcement. It is therefore possible that responders experience a more pronounced and rapid blunting of cigarette reinforcement due to NRT and varenicline nicotinic receptor occupancy than do non-responders, which ultimately lessens the reinforcing potential of cigarettes. Furthermore, only about a third of patients who use varenicline or NRT are positive responders, suggesting the majority of smokers trying to quit receive sub-optimal treatment [33].

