### Randomisation, allocation concealment and sequence generation

Participants who fulfil entry criteria and who have not responded to 2 weeks of varenicline as detailed below will be randomly allocated in a 1:1 ratio by a central computer to one of the two study groups, using block randomisation with varying block sizes. The randomisation sequence will be prepared by the study statistician and loaded into a secure database.

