**Table 1 Tab1:**
[figure not shown]
Schedule of enrolment, interventions, and assessments

*COPD* Chronic Obstructive Pulmonary Disease, *MH* Mental Health, *EC* E-cigarette

^1^Only in those allocated to the varenicline + EC group

The research assistant will phone participants two weeks after they have started their treatment, to assess their response to varenicline. Those who are varenicline responders (i.e. they have quit smoking or reduced the number of cigarettes smoked per day by > 50%) will be advised to continue their use of varenicline for another 10 weeks and to contact Quitline and/or a health professional (general practitioner or head clinician) for on-going smoking cessation behavioural support. Responders will not progress further in the study but simply continue on with their course of varenicline. Varenicline non-responders (i.e. those who are still smoking and have not reduced the number of cigarettes smoked per day by ≥50%) will be randomised to one of two treatment arms: 10 weeks of continued varenicline use (*n* = 169) or 10 weeks of continued varenicline use plus 18 mg/mL nicotine EC (n = 169) (Table 1).

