## Discussion

The STATUS trial will be unique in that it is one of the first trials to evaluate a highly practicable, adaptive treatment approach to smoking cessation among smokers with mental illnesses and/or AOD addictions. Current evidence suggests that combining varenicline with NRT (including ECs with nicotine) increases quit rates over varenicline alone, whilst the efficacy of nicotine ECs may be enhanced when used in addition to varenicline. However, these approaches to treatment have not been integrated or trialed among people with mental illnesses and/or AOD addictions who are varenicline non-responders. The findings will be of wide interest given the universal difficulty in helping smokers with such problems to quit. Such people are often excluded from smoking cessation trials with an efficacy goal. If positive, our findings will provide healthcare providers with a simple yet effective tool to increase smokers’ chances of successful cessation via adapting treatment based on self-reported initial response. In addition, if positive, this approach could lead to significant cost savings via reducing medication waste in non-responders (who would otherwise continue with an ineffective treatment). The trial is currently ongoing; recruitment started on 31/05/2017, with recruitment expected to take 18 months. Trial findings are likely to be available July 2019.

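### The run-in enrolment target of 507 does not follow from the stated 30% uptake and 80% non-response, which require about 1,409 enrolled to randomise 338

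*Protocol article*

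**What the plan says.** The Sample size section of the protocol article sets the randomised number first: "A sample size of 338 (169 in each arm) anticipates a 30% loss-to-follow-up", with 80% power at two-sided 0.05 for a 15-point difference and 30% abstinence expected in the combination arm.

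It then works back to enrolment with two rates:

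- Uptake: "We estimate 30% of participants will collect and use the prescribed varenicline for the first 2 weeks of the study".
- Non-response among those users: "most (around 80%) of this group will be varenicline non-responders after 2 weeks of medication use".

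The conclusion drawn from these is "Thus, 507 people will need to be recruited into the" initial treatment phase so that 338 can be randomised. The same paragraph allows 16 months for recruiting the 338.

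Three other places bear on this:

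- The section on randomisation, allocation concealment and sequence generation says that participants "who have not responded to 2 weeks of varenicline as detailed below will be randomly allocated in a 1:1 ratio".
- The text under Table 1 says: "Responders will not progress further in the study but simply continue on with their course of varenicline".
- The Background states that "only about a third of patients who use varenicline or NRT are positive responders", and the Discussion describes the trial as under way "with recruitment expected to take 18 months".

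**The concern.** The word that introduces 507 presents it as the result of the two rates just given. Multiplied together, those rates let about a quarter of enrolled people reach randomisation, whereas 507 for 338 needs two thirds of them to do so.

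Only run-in non-responders are randomised, so the run-in yield decides how many people must be enrolled and how long that takes. If the flow is as predicted and enrolment is planned and resourced for 507, the trial ends far short of 338 randomised and of its stated power. Recruitment had already begun when the article was written, so the target is in use.

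**Working it through.** **Inputs** (Sample size section unless noted): 338 to be randomised, 169 per arm; uptake 0.30; non-response among users 0.80; abstinence 30% in the combination arm and hence 15% on varenicline alone; two-sided 0.05; power 80%; loss to follow-up 30%; 16 months of recruitment (18 in the Discussion).

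**1. The randomised number reproduces.** The unpooled two-proportion formula gives

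n per arm = (1.960 + 0.842)² × (0.15 × 0.85 + 0.30 × 0.70) / 0.15² = 117.7, so 118.

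Allowing for loss: 118/0.70 = 168.6, so 169 per arm and 338 in total. The pooled formula gives 121 per arm, then 173 per arm and 346 in total, which is close.

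**2. The enrolment number does not.** Enrolled = randomised / (uptake × non-response).

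- Yield as stated: 0.30 × 0.80 = 0.24.
- Needed: 338/0.24 = 1,408.3, so 1,409.
- Yield implied by the target: 338/507 = 66.7%.
- Randomised from 507: 507 × 0.24 = 121.7, about 122 (61 per arm).
- Ceiling at 30% uptake, if every user were a non-responder: 507 × 0.30 = 152.
- Reading *around 80%* as 75% to 85%: 338/0.225 = 1,502.2 and 338/0.255 = 1,325.5, so 1,503 down to 1,326.

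**3. Other readings.**

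| Reading | Enrolment needed | Randomised from 507 |
|---|---|---|
| As written: 30% use, 80% of users non-responders | 338/0.24 → 1,409 | 122 |
| 30% is the share *not* using | 338/(0.70 × 0.80) → 604 | 284 |
| 507 counts only people who take varenicline | 338/0.80 → 423 | 406 |
| Non-users are also randomised as non-responders | 338/(0.70 + 0.24) → 360 | 477 |

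None returns 507. Three sums do: 338/(2/3), 338 × (1 + 0.30 + 0.20) and 3 × 169. The first would mean full uptake with one third responding, the second adds losses instead of dividing by retention, and the third might be a remnant of the dropped bupropion arm. The article does not show which, if any, was used.

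**4. Power if enrolment stopped at 507 and the flow were as predicted** (pooled two-proportion test, two-sided 0.05):

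| Scenario | Per arm | Rates compared | Power |
|---|---|---|---|
| As written, no loss | 61 | 15% v 30% | 51% |
| As written, 30% lost and left out | 43 (0.70 × 61) | 15% v 30% | 38% |
| As written, 30% lost and counted as smokers | 61 | 10.5% v 21% (0.70 × each rate) | 35% |
| 30% is non-use, 30% lost and left out | 99 (0.70 × 142) | 15% v 30% | 72% |

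**5. Enrolment pace over 16 months.** 1,409/16 = 88 per month, against 507/16 = 32 per month. Over 18 months the figures are 78 and 28.

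**The case against.** The strongest reply is that the trial is sized by the number randomised. The article describes 507 as what is needed to obtain 338, and nothing caps run-in enrolment there. If the yield is lower, the natural response is to enrol more people or take longer, and the design, analysis and power at 338 are untouched. That stands, and it means the power figures are conditional on stopping at 507 with the predicted flow. It does not make the enrolment target right, and a trial with a fixed recruitment period cannot assume that nearly three times the enrolment is available.

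Second, some readings are kinder. If 507 counts only people who start varenicline, 423 suffice. The text under Table 1 defines non-responders by smoking alone, so non-users who keep smoking might also qualify, which brings the need down to 360. Both are possible. The first, however, conflicts with applying the 30% to participants and then deriving 507 from it, and the second conflicts with the requirement of non-response to two weeks of varenicline. Neither gives 507. They do show that the figure of 122 belongs to the text as written and is not a forecast.

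Third, the secondary points are weaker. The one third of responders in the Background concerns users of varenicline or NRT in general, so it can differ from this trial's 20% without error. The 18 months in the Discussion could be an updated forecast. The fall from 38% to 35% power comes from counting the lost as smokers, a rule that would lower power at any sample size. All three objections are fair, and the finding does not depend on these points.

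**Conclusion.** The concern holds. As written, the two stated rates require about 1,409 people in the initial treatment phase, 2.8 times the stated 507, and 507 would lead to about 122 randomised, 36% of the 338 planned. If the 30% was a slip for non-use, the need is 604 and 507 falls 16% short (284 of 338).

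That 507 does not follow from the stated rates is certain, since it rests only on figures printed in one paragraph. The size of the shortfall depends on which meaning of 30% was intended, and the loss of power also depends on enrolment ending at 507. The randomised sample size itself is not in question. How 507 arose is unknown and does not matter to the conclusion.

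This must be fixed, because the recruitment plan and the feasibility of 338 rest on the figure.

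**What to change.** - State what the 30% means, and recompute the enrolment target by dividing 338 by uptake × non-response: 1,409 for 30% use, or 604 for 70% use, each with 80% non-response.
- Say whether people who never collected or used varenicline can be randomised, since the target depends on it.
- Explain why the planned 80% non-response differs from the one third of responders quoted in the Background, or use one rate in both places.
- Replace the assumed rates with the run-in flow observed so far, and give a single recruitment period in the Sample size section and the Discussion.
- If 338 randomised cannot be reached, state the number that can and the power it gives.

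The cost is a correction of text and planning figures. The target or the timeline will look less favourable, but no trial procedure changes.
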